### Trial status

3.5

This study respects World Medical Association Declaration of Helsinki on ethic in medical research and received approval by Ethical Committee of the UH Brno, Czech Republic. This trial inclines to SPIRIT 2013 checklist standards of reporting trials and is registered at Australian New Zealand Clinical Trial Registry with registration number: ACTRN12618001170213.

## Discussion

4

Despite the fact that CR brings great benefits as a prevention of cardiovascular diseases,^[26,27]^ the regular outpatient training provided by health insurances is insufficient and physical fitness of patients usually gets worse after being discharged from the hospital.^[28]^ There are a lot of reasons why these patients refuse to train on their own. Besides the financial point of view (high expenses on individual coach), there are also problems in motivation, technical, and social issues.^[29]^ The average age of patients diagnosed with CAD is 60.4 ± 10.9 years.^[24]^ These people often suffer from depression of low mood coming from their disease and are afraid to manage their physical exercises themselves.^[13]^

Fast developing technology allows us to search for new possibilities. What we need to do is to find out how to use them in modern medicine. It is the telemedicine which has already been practiced and explored in many countries. For the Czech Republic, this way of remotely controlled patient is still unexplored and unique.

Already published foreign studies show how useful, low-cost, and successful telemedicine could be,^[30,31]^ some of them talk about even better results reached by telemedicine than center-based trainings.^[32]^ To distinguish from previous studies, we decided to try a new, in our country available tool—a wrist sport tester. Data transport from patients to physiotherapist is provided via Internet connection.

The aim of this study is to monitor 2 groups of patients (ROT and ITG groups) who will undergo a 12-week training. The ROT group will be monitored under the direct supervision by a physiotherapist in a hospital; the ITG will be monitored and checked via wrist sport tester during their home-based exercise trainings. What we focus on in our study is to compare the improvement of their quality of life and physical fitness. We expect that the improvement of both variables after 12 weeks of training will be statistically significant in both ROT and ITG groups.

In this way, we want to show how efficient and successful telemedicine is and suggest its usage in other fields of modern medicine where we can observe not only short-term but also mainly long-term and sustainable effects. Results of this study will be useful not only for UH Brno, Czech Republic, but also for other medical centers which have not been working with telemedicine yet. As the topic of telemedicine is quite new and unexplored in the Czech Republic, we would like to open a discussion about future possibilities. The results of our study could be the best way to begin.

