## Abstract

**Background::**

Cardiovascular diseases remain the most common causes of death in the world. Instructions for secondary prevention recommend multifaceted approach in cardiovascular diseases risk management. Center-based physical exercise training is considered as an important integral part of cardiac rehabilitation (CR). Despite all recognized benefits CR brings, active interest of patients remains low in many countries, including the Czech Republic. That is why there is a need to focus on more effective patients’ participation in CR with respect to their preferences and needs. One of possible approaches is using telemonitoring guidance based on obtaining data via technological equipment during home exercise training. The aim of this study is to compare effectiveness of both center- and home-based exercise training with focus on participants’ physical fitness and quality of life.

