## Methods

2

Participants of CR-GPS project, as a single prospective randomized controlled trial, will be the patients of University Hospital (UH) Brno, Czech Republic, above the age of 18, diagnosed with CAD (angina pectoris, myocardial infarction, patients after coronary revascularization) in the last 6 months, with left ventricular ejection fraction >45%.

All eligible patients will be recommended by physiotherapists and research assistants from UH Brno. They must be clinically stable, able to undergo CPX, understand and write in Czech, and agree to participate in this project. Due to a random separation into 2 groups, all of them must have a mobile phone and free access to Internet connection.

Patients participating in CR-GPS will be further classified by cardiologist according to following criteria:No significant cardiovascular riskNo implanted cardioverter-defibrillator or pacemakerNo residual partial coronary artery stenosis requiring revascularizationNo orthopedic or neurological disability to exerciseNo mental disadvantage making cooperation impossibleNo serious oncological disease or treatment

During CR-GPS, some health problems might occur. If physical status of any participant changes significantly, he or she will be examined by the cardiologist who might change the medication. If this health problem becomes serious, this patient will be excluded from the trial. The obtained data of such patient will be further secured but not involved in final statistical evaluation.

According to Vysoký et al's study,^[24]^ number of participants calculation will be based on the improvement of peak VO_2_ 3.2 mL/kg/min with standard deviation 4.2 mL/kg/min. We will need 56 participants to reach 80% of statistical power with significance level set at *P* < .05. We count with 10% participant loss during the trial.^[25]^

At the beginning of the trial, all participants undergo baseline assessment on cycle ergometer (Ergoline Ergoselect 100, Bitz, Germany) and cardiologist will test their physical fitness through CPX. After that, they obtain a study package containing personal data questionnaire (sex, age, weight, diagnosis, pharmacological treatment), list of trial information, and informed consent form.

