### Statistical analysis

3.4

Baseline characteristics assessed from the questionnaire will be summarized using descriptive statistics. A paired *t* test will be used to find out whether there are statistically significant changes between baseline and final physical fitness values and values describing health-related quality of life. Between-group differences in physical fitness values will be evaluated by analysis of variance (ANOVA). Training adherence data will be expressed as percentage. For all statistical comparisons, the significance level will be set at *P* < .05. Analyses of all metric data (ANOVA and paired *t* test) will be processed in the statistical software Statistica 12.

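### The aim is to compare home with centre training, but the only stated hypothesis is a significant before-after gain in each arm; the between-arm ANOVA has no hypothesis or margin, and quality of life has no named between-arm test

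*Protocol article*

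**What the plan says.** The Background of the Abstract gives a comparative aim: "The aim of this study is to compare effectiveness of both center- and home-based exercise training with focus on participants" (the sentence goes on to fitness and quality of life). Section 2.1.3 agrees: the main outcome is a comparison of fitness in the two groups, at baseline and 12 weeks.

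The only hypothesis stated in words is in section 4 and concerns each arm by itself: "We expect that the improvement of both variables after 12 weeks of training will be statistically significant in both ROT and ITG groups". The next paragraph opens: "In this way, we want to show how efficient and successful telemedicine is".

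Section 3.4 names two tests. A paired t test is to look for "statistically significant changes between baseline and final physical fitness values and values describing health-related quality of life". A between-group ANOVA is planned for physical fitness. No direction, between-arm hypothesis or margin goes with the ANOVA, and no between-arm test is named for quality of life, although section 4 lists both outcomes among the improvements to be compared.

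On sample size, section 2 says "We will need 56 participants to reach 80% of statistical power", based on an improvement of "3.2 mL/kg/min with standard deviation 4.2 mL/kg/min".

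**The concern.** The aim and the hypothesis ask different questions. The aim asks how home training compares with centre training. The hypothesis asks whether each arm improves over its own baseline, and the answer can be yes in both arms whatever the difference between them.

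A within-arm gain is also weak evidence about training. Patients enter within six months of a coronary diagnosis and both arms exercise for 12 weeks, so there is no untrained group. A before-after gain can contain natural recovery, familiarity with the exercise test and regression to the mean as well as training. Only the randomised contrast removes what the arms share.

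Without a between-arm hypothesis, the article does not say what its ANOVA could establish. A non-significant result is not evidence of equal effect. At stake is whether two significant paired tests and a non-significant ANOVA would be presented as success for home training when it had delivered clearly less. For quality of life, the paired tests would be all there is.

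**Working it through.** **Inputs.** From section 2: improvement 3.2, SD 4.2, 80% power, N = 56, 10% loss. From the allocation paragraph: 1:1. From section 3.4: "For all statistical comparisons, the significance level will be set at *P* < .05". Two assumptions are mine: the tests are two-sided, and 4.2 is the SD of the change from baseline (the article does not say which SD it is). The ANOVA is treated as a two-group comparison of changes.

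**Reproducing the 56.** For a two-arm difference, n per arm = 2 × (1.960 + 0.842)² × 4.2² / 3.2² = 276.9 / 10.24 = 27.04, rounded up to 28, so 56 in total. This matches. A one-sided test gives 22 per arm (44), and a paired t test about 16 per arm (32). So 56 is a two-arm difference calculation that uses the whole 3.2 improvement as the difference between arms. That does not sit easily with an expectation that both arms improve.

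**When is the stated expectation met for fitness?** With 28 per arm:

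- Standard error of a within-arm mean change: 4.2/√28 = 0.794.
- Standard error of the between-arm difference: 4.2 × √(2/28) = 1.122.
- Paired-test power (noncentral t, 27 df): gain 3.2, 97.3%; gain 2.2, 76.2%; gain 1.6, 49.4%.
- The arms are independent, so P(both significant) is the product. For 3.2 and 1.6 it is 0.973 × 0.494 = 0.48.
- ANOVA power for a true difference of 1.6 (noncentrality 1.6/1.122 = 1.43, 54 df): 28.8%.
- The joint event in the last column was simulated with 100,000 trials per scenario.

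| True gain, centre / home | Both paired tests significant | ANOVA significant | Both significant, ANOVA not |
|---|---|---|---|
| 3.2 / 3.2 | 95% | 5% | 91% |
| 3.2 / 2.2 | 74% | 14% | 69% |
| 3.2 / 1.6 | 48% | 29% | 43% |

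The first and third rows share a pattern of results: equal arms produce it 91% of the time, and a home arm that has lost half the gain produces it 43% of the time.

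**Sensitivity.** With 25 per arm (56 × 0.90 = 50.4), the 3.2 / 1.6 scenario gives both significant 43% and ANOVA power 26%. With an assumed SD of change of 3.0 and 28 per arm, it gives 78% and 50%.

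**What a non-significant ANOVA leaves open.** The 95% CI half-width is t × 4.2 × √(2/n): 2.005 × 1.122 = 2.25 mL/kg/min at 28 per arm, and 2.39 at 25. Take a loss of 1.6 as an illustrative margin (the article gives none), truly equal arms and a one-sided 2.5% test. The power to exclude that loss is then 29% at 28 per arm and 26% at 25.

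**The case against.** The comparison is not absent. The two-group comparison is the declared main outcome, section 3.4 assigns between-group differences in fitness to ANOVA, and 56 reproduces as a two-arm calculation. A reader might infer that the plan discards its randomisation or permits no valid statement on home versus centre training. The documents do not support that for peak VO2.

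The sentence in section 4 is a forecast, not a success rule, and section 3.4 sets no criterion of significance in both arms. The link made in the following paragraph is also loose, since it could refer back to the study as a whole. Nor does the article say it will declare the arms equivalent or non-inferior, so that reading of a non-significant ANOVA is a risk and not a plan.

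Two stronger size claims also fail. One is that equal arms would often look different because only one paired test is significant. At the protocol's own gain of 3.2 this happens about 5% of the time (2 × 0.973 × 0.027). The figures of 50% and 28% need true gains of 1.6 and 2.4, which the article does not give as expected gains. The other is that home training could easily lose most of its benefit unnoticed. With a true loss of 70% (3.2 against 0.96), both paired tests are significant with a non-significant ANOVA 18% of the time.

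Finally, a margin or further tests might sit in an analysis plan not shown, and the closing software sentence of section 3.4 might be stretched to bring SF-36 under ANOVA. Neither removes the mismatch on the page: the one hypothesis the article states does not answer the aim it states.

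**Conclusion.** The point holds in a limited form. The stated hypothesis is within-arm and the aim is between-arm. The ANOVA of fitness is a valid randomised comparison, but with no hypothesis or margin a non-significant result cannot show comparability. For quality of life, only the paired test is named.

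The consequence is material. If home training delivers half of a 3.2 mL/kg/min gain, the stated expectation for fitness is still met about 48% of the time, and about 43% of the time this comes with a non-significant ANOVA. These figures rest on 4.2 being the SD of change, 28 evaluable patients per arm, two-sided 5% tests and normally distributed changes. A smaller SD makes the paired tests more often significant and also raises the power of the ANOVA.

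**What to change.** In section 3.4, and in section 4 in place of the sentence that begins with the expectation:

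- State the primary hypothesis on the between-arm difference in peak VO2, for example: *mean change in peak VO2 from baseline to 12 weeks differs between ITG and ROT*. A difference test is what the 56 reproduces.
- Draw the home-versus-centre conclusion, for peak VO2 and for the SF-36 scales, only from the between-arm difference with its 95% CI. Name that between-arm analysis for SF-36.
- Label the paired t tests descriptive, supporting no claim about home versus centre training or about the effect of training as such.
- State that a non-significant difference is not evidence of equal effect. Allow *comparable* or *not worse* only if the 95% CI excludes a margin in the outcome's own units, fixed and justified before any outcome data are seen. Fixing it only before data lock is too late in a trial where patients and care providers know the allocation.

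This costs wording only and needs no new data. The downside is a more modest permitted conclusion, since at this size the trial would seldom exclude even the illustrative loss of 1.6. If the sponsor wants a non-inferiority claim, it is no longer a wording change. With SD 4.2, 80% power and one-sided 2.5%, n per arm = 276.9 / margin², so the evaluable total is 140 for an assumed margin of 2.0, 218 for 1.6 and 554 for 1.0 mL/kg/min.
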